## Abstract

**Background:**

Stroke is a leading cause of disability, injury, and death in elderly people and represents a major public health problem with substantial medical and economic consequences. The incidence of stroke rapidly increases with age, doubling for each decade after age 55 years. Gait impairment is one of the most important problems after stroke, and improving walking function is often a key component of any rehabilitation program. To achieve this goal, a robotic gait trainer seems to be promising. In fact, some studies underline the efficacy of robotic gait training based on end-effector technology, for different diseases, in particular in stroke patients. In this randomized controlled trial, we verify the efficacy of the robotic treatment in terms of improving the gait and reducing the risk of falling and its long-term effects.

**Methods:**

In this single-blind randomized controlled trial, we will include 152 elderly subacute stroke patients divided in two groups to receive a traditional rehabilitation program or a robotic rehabilitation using G-EO system, an end-effector device for the gait rehabilitation, in addition to the traditional therapy. Twenty treatment sessions will be conducted, divided into 3 training sessions per week, for 7 weeks. The control group will perform traditional therapy sessions lasting 50 min. The technological intervention group, using the G-EO system, will carry out 30 min of traditional therapy and 20 min of treatment with a robotic system. The primary outcome of the study is the evaluation of the falling risk. Secondary outcomes are the assessment of the gait improvements and the fear of falling. Further evaluations, such as length and asymmetry of the step, walking and functional status, and acceptance of the technology, will be carried.

**Discussion:**

The final goal of the present study is to propose a new approach and an innovative therapeutic plan in the post-stroke rehabilitation, focused on the use of a robotic device, in order to obtain the beneficial effects of this treatment.

**Trial registration:**

ClinicalTrials.gov NCT04087083. Registered on September 12, 2019

## Background

According to data from “World Population Prospects: the 2017 Revision,” the number of older persons is expected to more than double by 2050 and to more than triple by 2100, rising from 962 million globally in 2017 to 2.1 billion in 2050 and 3.1 billion in 2100 [1]. Globally, the number of persons aged 80 or over is projected to triple by 2050 [2].

Stroke is a leading cause of disability, injury, and death in elderly people and represents a major public health problem with substantial medical and economic consequences [3]. The incidence of stroke rapidly increases with age, doubling for each decade after aged 55. Among adults aged 35 to 44 years old, the incidence of stroke is 30 to 120 of 100,000 per year, and for those ages 65 to 74, the incidence is 670 to 970 of 100,000 per year [4]. Annually, 15 million people worldwide suffer from stroke. Of these, 5 million die and another 5 million are left permanently disabled [5]. Three months after stroke, 20% of individuals remains wheelchair bound and 70% walks at reduced velocity [6]. Gait impairment is one of the most important problems after stroke and it is associated with difficulties in performing daily activities and in maintaining indoor and outdoor mobility. For this reason, improving walking function is often a key component of any rehabilitation program. To achieve this goal, a specific task-repetitive training seems the most promising one since, by increasing therapy dosage, intensity, and number of repetitions, the plasticity and the functional recovery are promoted [7–9]. To achieve this goal, gait machines were developed following exoskeleton [10, 11] or end-effector principles [12]. In the exoskeleton systems, there is a one-to-one correspondence between robots and human joints, and each single joint is guided along a preprogrammed trajectory. The end-effector systems use footplates or handles to generate a motion of the limb in space, as movements are generated from the most distal segment of the extremity and no alignment between patient-robot joints is required. On the basis of the support provided, the electromechanical devices can be also divided into inactive, passive, active-assisted, resistive, and interactive devices [13].

Several trials have been published regarding the use of these devices in stroke patients, but no differences were found between the two types of robotic gait machines [14]. Despite this evidence, some studies [15–18] underline the efficacy of robotic gait training based on end-effector technology, for different diseases. In particular, stroke patients, exposed to only robot-assisted end-effector-based gait training, showed significant improvements in global motor performance, gait endurance, balance and coordination, lower limb strength, and even spasticity.

Due to the incidence of the gait impairments after stroke and the low degree of acceptance of exoskeletons [19], we strongly believe that the efficacy of robotic rehabilitation treatments based on end-effector technology has to be deeply investigated.

### Study aims and objective

This study aims to evaluate an innovative rehabilitation treatment based on robotics, for the older subacute stroke patients, designed to improve the gait and to reduce the risk of falling. The treatment involves the use of the G-EO system (Reha Technology, Switzerland), an end-effector technology that simulates floor walking and stair climbing (up and down). The study objectives are:
To evaluate the effect of the rehabilitation treatment on the decrease of falling risk, evaluating balance and gait performance, of the elderly subacute stroke patients, as a result of the use of the G-EO system, at the end of the treatment and at 6 months, 1 year, and 2 years of follow-upTo evaluate the effect of the gait improvement by the gait speed evaluation on rehabilitation treatment on the gait speed of the elderly subacute stroke patients, as a result of the use of the G-EO system, at the end of the treatment and at 6 months and 1 and 2 years of follow-upTo evaluate the effect of the rehabilitation treatment on the fear of falling of the elderly subacute stroke patients, as a result of the use of the G-EO system, at the end of the treatment and at 6 months and 1 and 2 years of follow-up

In addition, the study design will include using standardized questionnaires and instrumental gait analysis, in order to collect data on the improvements with a mix-method approach.

## Methods/design

### Trial design

This study is a single-blind (outcome assessors) randomized controlled trial. In particular, the single-blind research method consists in not letting the researcher know the type of rehabilitation path assigned to each participant. Each subject will be assigned an identification code that will be known only to the assessor who will carry out the recruitment, the end of treatment, and the follow-up assessments. A total of 152 elderly subacute stroke patients will be recruited and randomly divided into two groups, to receive a traditional rehabilitation program or a robotic rehabilitation using the G-EO system in addition to the traditional therapy. Assessments will be performed at baseline, at the end of treatment, and 6 months, 1 year, and 2 years from the end of the treatment.

### Study setting

The study will be conducted at the Clinical Unit of Physical Rehabilitation, IRCCS INRCA, in the Ancona and Fermo branches, Italy. Assessments and treatments will be conducted in the robotics laboratories.

### Trial status

The protocol version number is 1 in date July 15, 2019.

At the time of the submission of this study protocol, data collection is ongoing; the first patient was enrolled on July 13, 2020. We expect to finish recruiting in 2 years.

### Participants

The inclusion criteria are:
Aged 65 and overCapacity to consentIschemic or hemorrhagic stroke within 3 months to the recruitment, proven by computerized axial tomography or nuclear magnetic resonanceFunctional Ambulation Category (FAC) score ≤ 2Rankin Scale score ≤ 3Complete communication and comprehension skills, assessed during the objective examinationAbility to stand upright, supported or unsupported, for 1 min [20]

The exclusion criteria are:
Failure to meet the inclusion criteriaConcomitant participation in other studiesSevere hypertonus of the hip, knee, and ankle of the paretic leg with a modified Ashworth scale score ≥ 3Severe hip, knee, or ankle contracture or orthopedic problem affecting ambulation that would preclude passive range of motion of the paretic legDeep vein thrombosis of the lower limbsOther cognitive, motor, and sensory deficits that negatively condition robotic trainingTreatment of spasticity of the lower limb within 3 months to the start of the study or during the studyLack of written informed consentClinical Dementia Rating (CDR) score ≥ 3Severe systemic diseases with life expectancy < 1 yearPatients unable to follow-up

### Sample size

In the study of Tramontano et al. [21], the Performance-Oriented Mobility Assessment (POMA) was evaluated in two groups of stroke patients, the cases were treated through an intervention based on visual-spatial training, and the assessments were detected in 2 stages (baseline and follow-up).

POMA [22], a test widely used to assess walking ability and associated with equilibrium, was used to calculate the sample size [23]. Assuming a small effect size of 10% [24], a statistical power of 80%, a significance level of 0.05, a correlation among repeated measures of 0.5, and that sphericity is exactly met, it is estimated that the overall sample size needed to capture this effect size is of 122 subjects, two groups, and 5 repeated assessments (a baseline and 4 follow-ups) in an ANOVA model within-between interactions. Even assuming a 20% drop-out rate, the total number required would be 152 subjects (76 for each arm). The GPower (Heinrich-Heine-Universität Düsseldorf, Düsseldorf, Germany) software was used to estimate this sample size.

For the secondary outcomes, we assumed an improvement of 12% and 15% for gait speed and fear of falling, respectively. These increases have been hypothesized on the basis of articles [25, 26] that identify an improvement in these parameters using a treatment comparable to that used in this protocol.

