### Outcomes

All outcome measures follow a standardized operating procedure. Table 1 shows the primary outcome and the secondary outcomes with the expected result at the end of the treatment. The expected improvement was derived from the analysis of similar studies [24], collected for the evaluation of the sample size for each outcome.

**Table 1 Tab1:** Outcomes and clinical assessments

Outcome(s)	Clinical assessment	Expected improvement at the end of treatment (%)
Primary: Decrease of falling risk	POMA	10
Secondary: Gait improvement (increase in walking speed)	Gait speed (gait analysis)	12
Secondary: Decrease of fear of falling	FES-I Short form	15

*POMA* Tinetti’s Scale or Performance-Oriented Mobility Assessment, *FES-I* Short Falls Efficacy Scale—International

Further evaluations will be carried out as follows:
Length and asymmetry of the semi-step, through instrumental gait analysisWalking and functional status through the Functional Ambulation Category and Barthel Index scaleAcceptance of the technology, through a UTAUT questionnaire

A summary of all data collected and when these are collected is provided in Table 2.

**Table 2 Tab2:** Schedule of assessment and outcome measures

Outcome	Clinical assessment	R	T1	FW1	FW2	FW3
Cognitive state	Mini-Mental State Examination	✓				
Gait parameters	Functional Ambulation Category	✓	✓	✓	✓	✓
Disability state	Rankin Scale	✓				
Cognitive state	CDR	✓				
Functional state	Barthel Index	✓	✓	✓	✓	✓
Spasticity state	Modified Ashworth scale	✓				
Quality of life	SF-12 Health Survey	✓	✓	✓	✓	✓
Sociodemographic characteristics	Check-list	✓				
Motor ability	Motricity index	✓	✓	✓	✓	✓
Attitude to technology	Assistive Device Predisposition Assessment – Scala E	✓				
Fall risk	Scala di Tinetti	✓	✓	✓	✓	✓
Gait parameters	Gait analysis + instrumental postural analysis	✓	✓	✓	✓	✓
Fear of falling	Short Falls Efficacy Scale—International	✓	✓	✓	✓	✓
Acceptance of technology	Psychosocial Impact of Assisted Device Scale (PIADS)		✓			

*R* recruitment, *T1* end of treatment, *FW1* first follow-up at 6 months since the end of treatment, *FW2* second follow-up at 1 year since the end of treatment, *FW3* third follow-up at 2 years since the end of treatment

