### Data analysis

The ITT approach will be adopted. Descriptive statistics will be used to describe the patients’ characteristics at baseline, compare the POMA values, the FES-I scores, and the gait speed in the two groups. Continuous variables will be expressed as mean values ± standard deviation. Categorical variables will be expressed as absolute values and relative frequencies. Independent samples’ t-tests and chi-squared test analyses will be used to compare both baseline characteristics and outcomes between groups. The primary efficacy analysis will be based on within-between group differences in the primary outcome measures (decrease in fall risk measured by POMA score) following 6 months of training with the G-EO system. The secondary outcome progression will be evaluated by comparing the measures of gait speed and FES-I scale from baseline to 6-month follow-up.

Comparisons for both primary and secondary outcomes will be repeated at each time point. Finally, repeated measures mixed models with interactions for each outcome will be performed in order to evaluate the effectiveness of the intervention. All tests for significance used a two-sided p-value of 0.05. Data were analyzed with STATA 15.1 (StataCorp, College Station, TX, USA).

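### The 80% power is for a standardised effect of f = 0.10 and is not shown for the 10% POMA improvement it is equated with

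*Protocol article*

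**What the plan says.** The Sample size section names POMA as the outcome used for planning and sets the inputs: "Assuming a small effect size of 10% [24], a statistical power of 80%, a significance level of 0.05", then "a correlation among repeated measures of 0.5, and that sphericity is exactly met". The design entered is "two groups, and 5 repeated assessments (a baseline and 4 follow-ups) in an ANOVA model within-between interactions". The result is 122 subjects, raised to 152 (76 per arm) for 20% drop-out, and the software is G*Power.

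Table 1 in the Outcomes section lists POMA with an expected improvement of 10% at the end of treatment. The text above the table connects that column to the sample size: "The expected improvement was derived from the analysis of similar studies [24], collected for the evaluation of the sample size for each outcome". The next paragraph of the Sample size section uses percentages in the same sense for the secondary outcomes, where "we assumed an improvement of 12% and 15% for gait speed and fear of falling, respectively". Both of those figures also stand in the Table 1 column.

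The only scale information for POMA is its maximum of 28 points, in the paragraph describing the instrument. The article gives no baseline mean, SD or target difference in points.

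**The concern.** One number from one reference does two jobs: it is the effect size in the power calculation and the percentage by which POMA is expected to improve. These are different quantities. The effect size for an ANOVA interaction in G*Power is Cohen's f, the SD of the interaction effects divided by the within-cell SD. A percentage change in POMA becomes an f only after it is turned into points, divided by an SD, and given a pattern over the visits.

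This calculation is the only justification for the sample size, and POMA is the primary outcome. As written, a reader will conclude that the trial has 80% power for a 10% improvement. If the result is null, that reader could take it as evidence against a 10% benefit, although the power for such a benefit has not been worked out.

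**Working it through.** **Inputs from the article.** Sample size section: k = 2 groups, m = 5 measurements, correlation ρ = 0.5, sphericity (ε = 1), α = 0.05, power 80%, effect *10%*. POMA description: maximum 28 points.

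**Step 1: reproduce 122.** Under the G*Power default for a within-between interaction,

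λ = f² · N · m · ε / (1 − ρ), df1 = (k − 1)(m − 1) = 4, df2 = (N − k)(m − 1).

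With f = 0.10 and N = 122, λ = 0.01 × 122 × 5 / 0.5 = 12.2 and df2 = 480. Power is 79.8% at N = 120, 80.2% at 121 and 80.5% at 122. So 122 is the first equal-arm total that reaches 80%, which matches the article exactly.

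The other readings tried do not match:

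| Reading of the input | N for 80% power |
|---|---|
| f = 0.10, default option, 5 visits | 122 |
| f = 0.10, 'as in SPSS' option | 302 |
| f = 0.10, 'as in Cohen' option | 300 |
| partial η² = 0.10 (f = 0.333) | 14 |
| d = 0.10 (f = 0.05) | 480 |
| f = 0.10, 4 visits | 138 |
| f = 0.10, 2 visits | 200 |

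**Step 2: what f = 0.10 means as an arm difference.** For two equal arms, f = ½ · SD over visits of δ(t) / σ, where δ(t) is the arm difference at visit t. Take no difference at baseline and a constant d at the four later visits. The mean difference is 0.8d. The SD over visits is √[(0.8² + 4 × 0.2²)/5] · d = √0.16 · d = 0.4d. Hence f = 0.2 · d/σ, and f = 0.10 means d = 0.5 SD. A simulation of 4,000 trials with 61 per arm and a sustained 0.5 SD difference gave 81% power, which confirms the conversion.

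The figure depends on the pattern:
- difference at one visit only: 0.50 SD
- difference at two or three of the five visits: 0.41 SD
- linear build-up, or linear fade to a quarter: 0.57 SD

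**Step 3: what 10% of POMA would give.** The SDs and baseline means here are assumptions, because the article has none. For a sustained difference, f = 0.2 × points / SD.

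| Meaning of 10% | Assumed SD | f | Power, N = 122 | Power, N = 152 |
|---|---|---|---|---|
| 2.8 points (10% of 28) | 4 | 0.140 | 98.5% | 99.7% |
| 2.8 points | 5 | 0.112 | 89% | 95% |
| 2.8 points | 6 | 0.093 | 74% | 84% |
| 2.8 points | 7 | 0.080 | 59% | 70% |
| 2.8 points | 8 | 0.070 | 46% | 57% |
| 1.5 points (10% of a baseline of 15) | 5 | 0.060 | 35% | 43% |
| 1.5 points | 7 | 0.043 | 19% | 23% |
| 1.0 point (10% of a baseline of 10) | 5 | 0.040 | 17% | 20% |
| 1.0 point | 7 | 0.029 | 10% | 12% |

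With 2.8 points, the stated 80% at N = 122 is met when the SD is about 5.6 or less (2.8 / 5.6 = 0.5 SD).

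**The case against.** Several counter-arguments carry weight.

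- **The article never writes f.** The authors may have picked the conventional f of 0.10 and loosely written it as 10%. That cannot be excluded, so the entry of f = 0.10 remains an inference. It does not rescue the text, because the Outcomes section itself ties the Table 1 percentages to the same reference and to the sample size.
- **An SD may exist elsewhere.** The article condenses a fuller protocol, and the cited studies are not at hand. One can say only that no SD is reported, not that none was used. An SD in another document would still not make an f of 0.10 and a 10% change the same quantity.
- **The word small is not an error.** It is the usual label for f = 0.10. A reader might infer that the authors mislabelled a moderate effect, but that judges f by the benchmarks for d. The label can mislead someone who thinks in arm differences, and no more than that.
- **Half an SD is not a fixed property of the design.** It holds for a sustained difference, and the plan assumes no time pattern.
- **A reader might infer that the trial is underpowered.** The document does not support this. Under the assumed values, power at N = 122 runs from 10% to 98.5%, so the question is open. N = 122 is also the cautious end: 152 are to be enrolled, and the mixed models named under Data analysis could use partial data from drop-outs.
- **The secondary-outcome percentages are weak support.** In the Sample size section they rest on other references, and no sample size is derived from them. They show only how the article uses percentages.

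**Conclusion.** The point stands as a fault in what the article claims, not in its arithmetic. The figure of 122 is right for f = 0.10 with five visits, ρ = 0.5 and sphericity. What is unsupported is reading the resulting 80% as power for a 10% POMA improvement. The two coincide only if 10% of POMA, on whatever base is meant, happens to yield f = 0.10. For a sustained difference that requires 10% to equal about half an SD.

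The conclusion rests on two things: the inference that f = 0.10 was entered, which is strong because no other reading tried returns 122, and the article's own link between the effect size and Table 1. The power figures for differences in points rest on assumed SDs and baseline means. They show how wide the uncertainty is and do not estimate the trial's actual power.

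**What to change.** In the Sample size section, state the target as a between-arm difference in POMA points, with an SD and its source and the assumed pattern over the five visits. The pilot trial mentioned under Data Availability may be a source for the SD. Derive f from these inputs, and restate power at 122 completers and at the 152 to be enrolled. In Table 1, say whether the 10% is a between-arm difference or a within-arm change, and of what base.

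If no SD can be found, remove the equation of the effect size with the 10% improvement. State instead that 122 completers give 80% power for f = 0.10, which is about 0.5 SD for a difference sustained at all follow-ups, and gloss the word small accordingly.

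The cost is a reworded paragraph, a clarified table entry and possibly a less favourable stated power. The correction itself needs no added patients.

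### The 80% power belongs to a five-assessment interaction test, but the analysis named as primary is the 6-month POMA comparison

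*Protocol article*

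**What the plan says.** The Sample size section of the protocol article lists its inputs: "Assuming a small effect size of 10% [24], a statistical power of 80%, a significance level of 0.05", together with "a correlation among repeated measures of 0.5, and that sphericity is exactly met". From these it arrives at "122 subjects, two groups, and 5 repeated assessments (a baseline and 4 follow-ups) in an ANOVA model within-between interactions". A 20% drop-out allowance brings the total to 152, or 76 per arm.

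The Data analysis section then states: "The primary efficacy analysis will be based on within-between group differences in the primary outcome measures", meaning POMA, and places this "following 6 months of training with the G-EO system". It provides t-tests for comparing outcomes between the groups and repeats the comparisons at every time point. Only after that does it add repeated-measures mixed models with interactions for each outcome. Those models are said to serve the evaluation of effectiveness but are not called primary. On significance: "All tests for significance used a two-sided p-value of 0.05".

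**The concern.** The sizing test and the test named as primary answer different questions. The first asks whether the two arms' POMA profiles differ in any way across five assessments. The second asks whether the arms differ in POMA at one visit. The five-assessment calculation draws on three assessments that a baseline-to-6-month contrast does not use, so its power figure does not carry over.

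Two things are at stake. A null 6-month result would be reported as coming from a trial with 80% power, a figure never derived for that comparison. And a reader cannot tell whether the 6-month contrast or the all-visit interaction decides efficacy, which leaves room to choose between them once results are known.

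**Working it through.** **Inputs.** From Sample size: two equal groups (k = 2), m = 5 assessments, power 80%, alpha 0.05, correlation rho = 0.5, sphericity met. The 10% effect size is read as Cohen's f = 0.10, a reading that reproduces the printed 122. From Data analysis: two-sided testing, primary comparison at 6 months.

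**Step 1: reproduce 122.** For a within-between interaction with noncentral F:
- lambda = f² × N × m / (1 − rho); df1 = (k − 1)(m − 1); df2 = (N − k)(m − 1).
- N = 122, m = 5: lambda = 0.01 × 122 × 5 / 0.5 = 12.2; df = 4 and 480; power 80.5%.
- N = 120 gives 79.8%, so 122 is the smallest equal-group size reaching 80%.
- Drop-out: 122 / 0.8 = 152.5, against 152 printed; the difference is immaterial.

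The printed figure is correct for the test it describes.

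**Step 2: what f = 0.10 implies at 6 months.** Let D be the between-arm difference at each assessment in SD units. With two equal groups, f = ½ × √(mean of (D − mean D)²). The article states no pattern for D, so the patterns below are assumptions, in the order baseline, end of treatment, 6 months, 1 year, 2 years.
- Sustained, (0, d, d, d, d): the mean square is 0.16d², so f = 0.2d. Setting f = 0.10 gives d = 0.50 SD at 6 months.
- Peak at end of treatment, then decay, (0, d, 0.75d, 0.5d, 0.25d): the mean square is 0.125d², so f = 0.177d and d = 0.566. At 6 months the difference is 0.75 × 0.566 = 0.424 SD.
- Two occasions only, (0, d): the mean square is 0.25d², so f = d/4 and d = 0.40 SD.

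**Step 3: power of the 6-month contrast, 122 analysed (61 per arm).** With rho = 0.5 the SD of the change score is SD × √(2 × (1 − 0.5)) = SD. A t-test on 6-month values and one on change from baseline therefore have the same power. The noncentrality is D × √(61/2), with 120 df.

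| Assumed meaning of f = 0.10 | D at 6 months | Noncentrality | Power |
|---|---|---|---|
| Sustained effect | 0.50 SD | 2.76 | 78% |
| Peak, then decay | 0.42 SD | 2.34 | 64% (63% at exactly 0.42) |
| f applied to two occasions | 0.40 SD | 2.21 | 59% |

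The last row agrees with the interaction formula at m = 2: lambda = 0.01 × 122 × 2 / 0.5 = 4.88, df = 1 and 120, power 59.2%. On that row, analysing all 152 gives 69%, and 80% power would need 200.

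**Step 4: with baseline adjustment.** Adjusting for baseline POMA at rho = 0.5 multiplies the residual SD by √(1 − 0.25) = 0.866. With 122 analysed:
- 0.40 SD: 0.40 / 0.866 = 0.462, power 72%.
- 0.44 SD: 0.44 / 0.866 = 0.508, power about 80% (79.5%).
- 0.50 SD: 0.50 / 0.866 = 0.577, power 89%.

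**The case against.** A reader might infer that the trial really has only 59% power, or needs 200 evaluable patients. The article does not support that. Cohen's f depends on the number of occasions: holding f = 0.10 while going from five assessments to two shrinks the implied difference from 0.50 SD (sustained effect) to 0.40 SD. Setting 80.5% beside 59% therefore compares a larger effect with a smaller one. At 0.50 SD the 6-month contrast has 78%, a loss of about two points. The article leans towards the sustained pattern: Table 1 places the expected POMA gain at the end of treatment, and the Discussion describes the later visits as monitoring whether gains are retained. That is suggestive, not a stated assumption, but it also tells against much lower figures obtained by letting the benefit grow over two years.

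Three further points have weight:
- The drop-out allowance covers follow-up to 2 years, so more than 122 may be available at 6 months. At 0.50 SD, 130 analysed gives 81% and 152 gives 86% without adjustment.
- The primary analysis is loosely worded. The baseline-to-6-month interval is spelled out only for the secondary outcomes, and the phrase within-between echoes the sizing section. Naming the mixed-model interaction as primary would also remove the mismatch.
- An omnibus interaction alone would not locate the difference, but the planned visit-by-visit comparisons partly answer that.

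These points limit the size of the problem. They do not remove it: the article calls the 6-month comparison primary and computes power for another test.

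**Conclusion.** The mismatch stands and should be fixed. It is a failure of alignment, not an arithmetic error, since 122 reproduces. For the named 6-month test with 122 analysed and no baseline adjustment, power is about 59% to 78% across the three readings of f = 0.10 examined, and near the top of that range if the effect is conserved after treatment. No single figure can be asserted, because the article gives neither an SD nor a pattern over time. For the same reason the 10% in Table 1, an expected improvement in POMA, cannot be converted into f = 0.10. All results rest on rho = 0.5 and equal arms, as the article assumes. The case for correction does not depend on which pattern is true: the claimed 80% was derived for a different test.

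**What to change.** Keep 152 and make Sample size and Data analysis describe the same primary test. The preferred choice is the between-arm difference in POMA at the 6-month visit, adjusted for baseline POMA, which Table 2 shows is already collected. Baseline adjustment is a recommendation here; the article does not name it.

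Replace the 80% statement with the power of that test and its assumed difference in SD units. With 122 analysed and rho = 0.5 this is 72% at 0.40 SD, about 80% at 0.44 SD and 89% at 0.50 SD. Keep the mixed-model interaction as supportive. If the interaction was meant as primary, say so instead and make the 6-month comparison secondary.

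Name the primary visit unambiguously. The wording "following 6 months of training with the G-EO system" does not match the 7-week course under Intervention or the Table 2 visits, which are counted from the end of treatment, so these passages must be reconciled.

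The cost is rewording two paragraphs, with no added patients or visits. The stated power may become less favourable. Trial status reports enrolment as ongoing, so the change should be settled before outcome data are analysed.
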